### Recruitment

Once eligibility criteria have been checked, patients from French comprehensive cancer care centers or hospitals will be invited to join the study.

Before inclusion, patients should read and understand the study information letter and then should date and sign the informed consent form (ICF) to allow them to join the study.

The coordinating center will be notified of each inclusion before completion of the first QoL questionnaire (inclusion document will be completed and returned to Paul Papin Center, Angers by fax).

Since eligibility criteria will be checked and patients' ICF will be collected, the first QoL questionnaires and the test-retest (3 days after the first completion) will be completed (before randomization) in the following order: QLQ-C15 PAL, MVQOLI, and QUAL-E.

After completion of the retest QoL questionnaire, the eligibility criteria and date of signed informed consent will be collected on a dedicated internet site to allow e-randomization with a personal log-in and password (Tenalea software). The study coordinator will then be able to randomize patients. The allocated arm will be sent to investigators, to the methodologists, the principal investigator and the coordinating center by email.

Patients will be randomized after the test-retest to limit the number of non-assessable patients for reproducibility.

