### Randomization

To explore secondary objectives 3 and 4 using a factorial design, QoL questionnaire order, and spontaneous QoL completion will be randomized 1:1:1:1 using a minimization technique stratified according to center, cancer location, sex, and age.

Patients will be randomized in one of the following four arms (Table 1): (1) Arm A: MVQOLI then QLQ-C15 PAUL and QUAL-E, evaluation every month; (2) Arm B: QLQ-C15 PAL, MVQOLI and QUAL-E, evaluation every month; (3) Arm C: MVQOLI then QLQ-C15 PAL and QUAL-E, evaluation every month and spontaneous QoL completion; and (4) Arm D: QLQ-C15 PAL, MVQOLI and QUAL-E evaluation every month and spontaneous QoL completion.

**Table 1 T1:** Follow-up for QoL and data collection according to randomized arms

	Baseline		Follow-up	
	**D1^a^**	**Between** **D1 and D3^b^**	**Before every consultation until death (J30+/-3 days)**	**If necessary according to randomized allocated arm (notebook)**

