**Collected data and order of administration for QoL questionnaires**				

	**Arms**	**Arms**	**Arms**	**Arms**

Consent	A/B/C/D			

Questionnaires: QLQ-C15, MVQOLI and QUAL-E	A/B/C/D	A/B/C/D	B and D	

Questionnaires: MVQOLI, QLQ-C15 and QUAL-E			A and C	

Questionnaires: MVQOLI, QLQ-C15				D and C

Performance Status, Performance Palliative Scale	A/B/C/D	A/B/C/D	A, B, C, D	

Vital signs, pain (EVA)	A/B/C/D	A/B/C/D	A, B, C, D	

Care (Oncology, Psychology, and so on)	A/B/C/D	A/B/C/D	A, B, C, D	

Responsiveness question	A/B/C/D	A/B/C/D		D and C

^a^D1: First day, the day where the first QoL questionnaires will be completed; D3: 3 days after the first day administration

^b^Can be done D1 at the end of the day if the first was done early in the day

^c^Only MVQOLI and QUAL-E

The above randomization was chosen to explore methodological aspects to optimize QOL tools in the end-of-life setting.

It will allow us to assess the occurrence of an order effect on QoL level by investigating a halo effect and/or a framing effect. Since every patient should complete three questionnaires (MVQOLI, QUAL-E, and the QLQ-C15 PAL), completion of the first questionnaire could influence responses for the following questionnaires, resulting in different QoL levels. Moreover, this effect could be differential depending on the completion order. Since QUAL-E needs a face to face interview, it will be completed by the patient at the end for each arm.

The second randomization will investigate the added value of spontaneous QoL completion to capture clinically important changes in QoL that could have occurred between two planned QoL assessments.

For each allocated group a specific case report form (CRF) will be produced with the corresponding order of QoL questionnaires to prevent changes in completion order (that is, 'cross-over') after the randomization.

Furthermore, the date and time of completion for each QoL questionnaire will be collected. This will allow us to check the order of completion used by the patients.

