QoL will be described at each follow-up and compared at the inclusion (using Wilcoxon rank test) and then longitudinally analyzed using mixed model analyses of variance for repeated measurement [39-41] to test for the following: a therapeutic strategy effect whatever the follow-up; time effect whatever the therapeutic strategy; interactions between therapeutic strategy and follow-up; and effects of other clinical factors. The best model will be chosen according to the smaller Akaike's information criterion (AIC).

As for the TUDD approach, it will be compared with Log-Rank tests. Univariate and multivariate Cox analyses will be done to compute hazard ratios with 95% CI.

3. To assess the added value of spontaneous QoL completion to detect a clinically significant change in this setting

The proportion of patients who report at least one MCID during follow-up using the Jaeschke transition question will be compared according to the group allocated by randomization using univariate and multivariate logistic regressions.

We will also compute effect size (ES) and standardized response mean (SRM) to explore sensitivity to change according to spontaneous completion of a QoL questionnaire or not. We aim to demonstrate that with spontaneous completion of QoL questionnaires, ES and SRM will be improved.

For the sensitivity analysis, time to definitive QoL deterioration will also be estimated including this spontaneous completion of QoL questionnaires.

Analyses will be performed on an intent-to-treat principle.

4. To assess the effect of questionnaire order on QoL levels Longitudinal QoL analyses will be done as described above QoL will be described at each follow-up and compared at inclusion and then longitudinally analyzed using the mixed model analysis of variance for repeated measurements [39-41]. For the TUDD approach, it will be compared with Log-Rank tests. Univariate and multivariate Cox analyses will be done to compute hazard ratios with 95% CI.

Analyses will be performed on an intent-to-treat principle.

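### Objective 4 compares arms at inclusion, where all use the same order; no adjusted main analysis is named; and Table 1 gives one notebook sequence for arms C and D

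*Protocol article*

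**What the plan says.** **Order before randomization.** Under Recruitment, the first questionnaires and the retest "will be completed (before randomization) in the following order: QLQ-C15 PAL, MVQOLI, and QUAL-E". The same section adds: "Patients will be randomized after the test-retest to limit the number of non-assessable patients for reproducibility". Table 1 confirms one common order for arms A, B, C and D at both baseline assessments.

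**Order after randomization.** Under Randomization, arms A and C are allocated MVQOLI first, and arms B and D QLQ-C15 PAL first. QUAL-E is last in all arms. Allocation is 1:1:1:1, "using a minimization technique stratified according to center, cancer location, sex, and age".

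**Analysis of order (objective 4, under Longitudinal analyses).** "QoL will be described at each follow-up and compared at inclusion and then longitudinally analyzed using the mixed model analysis of variance". The text refers back to the longitudinal methods described earlier. Time until definitive deterioration (TUDD) is compared by log-rank test, and "Univariate and multivariate Cox analyses will be done to compute hazard ratios with 95% CI".

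**Analysis of spontaneous completion (objective 3, same section).** The proportion of patients reporting at least one minimal clinically important difference is compared by randomized group "using univariate and multivariate logistic regressions".

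**Notebook.** In Table 1, whose header says that it covers the order of administration, the notebook row reads "Questionnaires: MVQOLI, QLQ-C15" for arms D and C together. The text under the table promises a separate case report form for each allocated group, in that group's order, "to prevent changes in completion order". Completion of QoL questionnaire describes the patient booklet for arms C and D with QLQ-C15 PAL named before MVQOLI.

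**The concern.** Three separate matters bear on the two randomized questions.

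- A comparison of order groups at a time when the order was the same for everyone carries no information on order. Listed under the order objective, it invites a chance difference to be read as an order effect. If inclusion also entered the mixed model as an outcome time point in an overall order effect, it would dilute the contrast.
- Several analyses are named for each randomized question, some unadjusted and some multivariate, without saying which one counts. After minimization on prognostic factors, an unadjusted comparison tends to overstate the standard error. The pre-randomization scores are already collected and could sharpen the comparison of continuous scores.
- If the booklets were printed from Table 1, arm D would complete its spontaneous forms in arm C's order. That would mix the two randomized factors within arm D.

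**Working it through.** The article gives no power figure for the order effect, so there is none to reproduce. The check compares sections and adds illustrative arithmetic.

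**1. When do the orders differ?**

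| Assessment | Arms A and C | Arms B and D |
|---|---|---|
| First completion, before randomization | QLQ-C15 first | QLQ-C15 first |
| Retest, before randomization | QLQ-C15 first | QLQ-C15 first |
| Monthly follow-up | MVQOLI first | QLQ-C15 first |

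The expected order difference at inclusion is therefore zero, and a test there rejects at its nominal level. For m independent scores tested at 5%, the chance of at least one significant result is 1 − 0.95^m:
- m = 1: 5%
- m = 6 (for example, MVQOLI's five dimensions and total): 26%
- m = 12: 46%

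The 5% level and independence are assumptions. Positively correlated scores would give lower figures for m > 1.

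**2. What if inclusion were averaged into an overall order effect?** With K follow-ups, the average effect shrinks by K/(K + 1): to 50%, 67% and 75% for K = 1, 2, 3.

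For power, take 372/2 = 186 patients per order group and two-sided alpha 0.05. Assume an effect of 0.3 SD, a correlation of 0.5 between any two assessments (compound symmetry) and K = 2. The mean of k assessments has variance (1 + (k − 1) × 0.5)/k in SD² units.
- Inclusion averaged in: effect 0.3 × 2/3 = 0.20, variance (1 + 2 × 0.5)/3 = 0.667, power about 66%.
- Follow-ups only: effect 0.30, variance (1 + 0.5)/2 = 0.75, power about 92%.
- Follow-ups adjusted for baseline: effect 0.30, variance 0.75 − 0.5² = 0.50, power about 98%.

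Effect size, correlation and number of follow-ups are assumed. Attrition is ignored.

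**3. What could adjustment for the pre-randomization score gain?** Take reliability 0.65, the minimum ICC that the article requires, and assume a true-score correlation ρ of 0.7–0.8 between baseline and follow-up.
- One baseline score: r = 0.65ρ = 0.455–0.52, so r² = 0.21–0.27.
- Mean of test and retest: reliability 2 × 0.65/1.65 = 0.788 and r = ρ√(0.65 × 0.788) = 0.50–0.57, so r² = 0.25–0.33.

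Residual variance would fall by about 21–33% relative to a model that ignores baseline.

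**4. Which notebook order applies?**
- Allocation in Randomization: arm C has MVQOLI first, arm D QLQ-C15 PAL first.
- Table 1 notebook row: MVQOLI then QLQ-C15 for both, which fits C but not D.
- Completion of QoL questionnaire: QLQ-C15 PAL then MVQOLI for both, which, read as an order, fits D but not C.
- Text under Table 1: a form for each group in its own order, which no single sequence can satisfy for both arms.

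In Table 1's monthly rows the sequence of names is what separates A and C from B and D. Sequence therefore carries meaning in that table.

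**The case against.** **The order effect is not tested only at inclusion.** This stands. The same sentence goes on to the longitudinal mixed model, followed by the TUDD analyses, and both use assessments at which the orders differ. The article never calls the inclusion comparison a test of order. Very similar wording appears under objective 2, where therapeutic strategies are not randomized and a baseline comparison makes sense. Nor does it say that inclusion is an outcome time point in an overall order effect, so dilution is a risk of the wording and not a stated feature.

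**A reader might infer that the models leave out the baseline score and the minimization factors.** The article does not support that. It gives no covariate list for objective 4, plans multivariate models for objectives 3 and 4, allows for other clinical factors in the longitudinal model of objective 2, measures TUDD against the score at inclusion, and announces a statistical analysis plan before database lock. Silence on covariates is normal in a protocol article. What remains is that unadjusted and adjusted analyses are both named and neither is made the main one.

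**A reader might infer that every spontaneous form in arm D will be in the wrong order.** That does not follow either. The notebook row may list content only, and the group-specific form would override it. Date and time are recorded for each questionnaire, so the order used can be checked. Spontaneous forms are mentioned in the analyses of objective 3, not in the order analysis. The inconsistency between the sections still stands.

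**Conclusion.** The point holds in a limited form.

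- The comparison at inclusion under objective 4 is uninformative about order by design. This follows from the article alone. The false-positive rates and the 50–75% dilution show what misuse would cost; they do not describe what the plan commits to.
- Naming an adjusted main analysis for objectives 3 and 4 is an improvement that uses data already collected; it does not correct a stated omission. The gain of about 21–33% of residual variance rests on a reliability set at the required minimum and on assumed correlations. It applies only to continuous scores, not to objective 3's binary main endpoint, and would be smaller if the mixed model already draws on the baseline score.
- The notebook sequence is a literal inconsistency between Randomization, Table 1 and Completion of QoL questionnaire. Its effect depends on how the booklets were actually printed.

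None of this invalidates the follow-up analyses or the reproducibility endpoint.

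**What to change.** 1. Under objective 4, delete the comparison at inclusion or label it a descriptive balance check. State that the order contrast uses post-randomization assessments only, with the pre-randomization score as a covariate and not as an outcome time point in an overall order effect.
2. For objectives 3 and 4, name the adjusted model as the main analysis. It should contain both randomized factors, center, cancer location, sex and age, and, for continuous scores, the pre-randomization score (the mean of test and retest is available). Stratify or adjust the TUDD comparison for the minimization factors, and keep the unadjusted results as supportive.
3. Reconcile the Table 1 notebook row, the booklet description and the group-specific forms so that each arm's notebook follows its randomized order. Check any booklets already issued.

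The cost is wording in the analysis plan, one corrected table row and, if needed, one booklet template. No new data are required. The article reports 12 of 372 patients included at submission, so on that status few booklets would be affected.

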### Data management

Data will be collected on CRF. The principal investigator in each center will be responsible for his or her data. Then data will be computerized and validated with Capture System software (Clinsight, Cenon, France) according to the specifications defined for this study.

## Discussion

The aim of this validation study will be to allow the assessment of QoL at the end of life in order to improve care for cancer patients. At this stage of the disease, patients require the support of clinicians and other caregivers for discussion, for psychological support and exchange in order to improve satisfaction and wellbeing. This support could help patients to cope with the end of life. Life completion and preparation for death are essential for patients' wellbeing and QoL at the end of life [45]. In this context, an external intervention could help to improve QoL dimensions, especially dimensions related to function, emotional status, anxiety, depression, and preparation for the end of life [46]. Moreover QoL questionnaires could be used as a communication tool to facilitate discussion about difficult subjects that the patient and/or the clinician would not have approached spontaneously [47]. Furthermore, QoL evaluations at the end of life and related discussions could improve the use of therapies and could contribute to appropriate care strategies [1,48].

In this context, the absence of validated tools to assess QoL in French cancer patients at the end of life must be resolved. This is one of the major preliminary steps to evaluate QoL in these patients. If our study fails to confirm the psychometric validity of these translated tools, we may have to investigate the possibility of creating a specific QoL tool for French cancer patients at the end of life.

In this case the creation of a new QoL questionnaire for French cancer patients at the end of life will be supported by the '*Qualité de vie et cancer*' clinical research platform. This new tool will be developed in agreement with reference methodology.

We think that these specific questionnaires could be useful for the evaluation of therapeutic approaches in future clinical trials or for everyday use in palliative care units. The ultimate goal should be to improve QoL of these patients who are trying to cope with end-of-life concerns. The perceptions, expectations, and experience of patients as well as physicians collected during this study could serve to improve the use of these QoL tools.

## Trial status

Between December 15, 2010 and April 5, 2011 30 patients have been included in five centers to check the understanding of the questions as well as their acceptability. Qualitative analyses of these pre-test data confirmed that questionnaires and translations were acceptable and that the study is feasible. Rewording of some items was the only adjustment needed with respect to understanding of the translation.

At the time of submission of the manuscript, the longitudinal prospective study to cross-culturally adapt the English questionnaires QUAL-E and Missoula Vital Quality of Life Index (MVQOLI), and to validate their psychometric properties in the end-of-life setting is ongoing. Nine centers were open and active and 12 patients out of the goal of 372 have been included since November 8, 2011.

## Abbreviations

EoL: End of life; QoL: Quality of life; ICF: Informed Consent form; CRF: Case report form; CRA: Clinical research assistant; IC: Intraclass correlation coefficients; MCID: Minimal clinically important difference; PPS: Performance palliative scale; ANOVA: Analysis of variance; TUDD: Time until a definitive QoL score deterioration.
